## **4.2. Risk Assessment**

### **4.2.1. Risk of injecting study vaccines**

As with any vaccination, there is a potential risk of anaphylactic reaction to the vaccine administered in this study. Following vaccination, all subjects will be asked to remain in the hospital for at least 30 minutes to identify and address potential safety risks.

The potential risks to subjects during the clinical study of this product are mainly due to the common adverse events of vaccine injection, which are localized adverse events: pain, hardness, erythema, rash, swelling, itching, and cellulitis at the site of

---

vaccination; and systemic adverse events: fever (axillary warmth), diarrhea, nausea, vomiting, headache, myalgia (not at the site of vaccination), arthralgia, chills, anorexia, fatigue/weakness, and acute Allergic reaction. Generally resolves on its own without treatment. A few reactions are strong and will be closely monitored by the investigator and treated symptomatically.

#### **4.2.2. Antibody-mediated (infection) potentiation or vaccine-enhanced disease**

In some cases, antibodies may play a role in enhancing viral infection during viral infection by assisting viral entry into target cells and increasing the rate of infection, that phenomenon known as Antibody-Dependent Enhancement (ADE) or Vaccine Enhanced Disease (VED). Fc fragment-mediated ADE increases viral invasion. Both virus-antibody immune complexes and Th2 immune-biased responses can occur in cases of VED. Such phenomena have been observed in preclinical animal testing of a SARS vaccine (rhesus monkeys), and a vaccine that prevents respiratory syncytial virus-infected diseases in children.

To date, no ADEs and/or VEDs have been observed in preclinical or clinical studies with the study vaccine. All subjects, especially suspected or confirmed cases of COVID-19, will still be closely monitored and followed throughout the study to ensure subject safety. If a subject reports a suspected or confirmed case during the study, he/she will be required to go to the study-designated research center or hospital for hospitalization.

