## 6.6. Observation of protective efficacy

**7 days after the booster vaccination for every participant, the investigators need to carry out the following "routine monitoring" on the participants through a combination of remote visits and on-site visits:**

- The investigators remotely visit the participants to see if they have symptoms related to COVID-19;
- When the investigator learns that the participant has any one or more of the following conditions through remote visits, it is necessary to collect the participant's throat swab sample A1 (for SARS-CoV-2 nucleic acid or antigen detection), and further inquiry, record, and guidance should be done to the participant to continue to observe and record symptom types, start and end time, severity, etc. If an on-site visit is conducted to the participant (the on-site visit could be carried out by the participant going to the study site or the investigators' visit), another nucleic acid throat swab sample B1 (backup sample) needs to be collected:

④ *Any possible signs or symptoms related to COVID-19 appear (fever or chills, malaise/fatigue, headache, dry throat, muscle pain, sore throat, nasal congestion/runny nose, anorexia/nausea/vomiting, diarrhea, new sense of smell/dysgeusia, conjunctivitis);*

⑤ *Any one or more respiratory-related symptoms (cough, shortness of breath, or dyspnea) appear and last for any time;*

⑥ *Clinical or imaging evidence of pneumonia.*

**If the result of SARS-CoV-2 nucleic acid or antigen detection of the participant's throat swab sample A1 is positive, the investigators need to**

---

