**continue to carry out the following "case monitoring" on the participant:**

- Send the participant's nucleic acid throat swab sample B1 (if collected) to the central laboratory for SARS-CoV-2 variant strain type detection, and guide the participant to go to the designated hospital for chest imaging examination (chest CT) ;
- Provide necessary medical supplies to the participant, and continue to remotely visit him/her twice a week. Instruct the participant to observe and record symptoms and self-medication at home, or guide him/her to go to the designated hospitals for medical treatment according to the situation. If the participant has symptoms such as shortness of breath or dyspnea, guide him/her to detect blood oxygen saturation according to the situation. According to the symptoms recovery of the participant, conduct an on-site visit to collect a throat swab sample or antigen nasopharyngeal swab sample for SARS-CoV-2 nucleic acid or antigen detection, until the result of SARS-CoV-2 nucleic acid or antigen turns negative or the symptoms disappear or stabilize under the investigators' evaluation.
- Collect the participant's treatment and medical history to judge the severity of COVID-19, and make the records about the type, starting time, and reporting time of the participant's symptom, and the collection time, detection time, and reporting time of each nucleic acid sample, and the diagnosis time and outcome of the case, to form relevant records;
- Establish a COVID-19 case file for the participant, and fill in and report the first/follow-up COVID-19 case report according to the remote visit;
- On-site monitoring and medical monitoring teams need to conduct a preliminary review of the completeness, rationality, and logic of the COVID-19 case report, and raise necessary inquiries and requirements of information supplementary, then submit them to the investigators for diagnosis and judgment.

**If the result of SARS-CoV-2 nucleic acid or antigen detection in the participant's throat swab sample A1 is negative, the following retest should be continued:**

- 
- The participant's throat swab sample A2 (for SARS-CoV-2 nucleic acid or antigen detection) and sample B2 (backup sample) need to be collected again within 48 hours;
  - If the result of SARS-CoV-2 nucleic acid or antigen detection of the participant's throat swab sample A2 is positive, the above "case monitoring" process should be followed to carry out relevant work;

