### **11.3.2. Case surveillance**

**If the test result for SARS-CoV-2 nucleic acid or antigen in the throat swab sample A1 of the subject is positive, the researcher needs to continue to carry out the following "case monitoring" work:**

- Send the throat swab sample B1 of the subject's nucleic acid (if collected) to the central laboratory for SARS-CoV-2 variant typing testing, guide and coordinate the subject to go to a designated hospital for chest imaging examination (chest CT);
- Provide necessary medical supplies to the subjects, continue to conduct remote visits twice a week, guide them to observe and record symptoms and self-medication at home, or guide them to seek medical treatment at designated hospitals according to the situation; If the subject has symptoms such as Tachypnea or dyspnea, guide and coordinate the subject to detect blood oxygen saturation according to the situation; According to the recovery of symptoms of the subjects, conduct on-site visits, collect samples of nucleic acid oropharyngeal swabs or antigen Nasopharyngeal swab for SARS-CoV-2 nucleic acid or antigen detection until the results of SARS-CoV-2 nucleic acid or antigen turn negative

---

or the symptoms disappear or stabilize according to the evaluation of the investigator;

- Collect the treatment status and medical history of the subjects to determine the severity of COVID-19, record the type of symptoms, occurrence time, reporting time, collection time, testing time, reporting time, diagnosis time, and outcome information of each nucleic acid sample, and form relevant records;
- Establish a COVID-19 case file for the subjects, fill out and report the first/follow-up COVID-19 case report based on remote visits;
- The on-site and medical monitoring teams need to conduct a preliminary review of the completeness, rationality, and logic of the COVID-19 case report, raise necessary questions and information supplement requirements, and submit it to the researchers for diagnosis and judgment.

**If the test result of the throat swab sample A1 for SARS-CoV-2 nucleic acid or antigen is negative, the following retesting work needs to be continued:**

- Within 48 hours, the throat swab sample A2 (for SARS-CoV-2 nucleic acid or antigen testing) and sample B2 (backup sample) need to be collected again;

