### **12. Subject Safety and adverse event management**

#### **12.1. Adverse Event Definition**

Adverse Event (AE): it refers to all adverse medical events that occur after participants receive the vaccine/drug for the study, which can be manifested as symptoms, signs, diseases, or laboratory test abnormalities, but are not necessarily related to the study vaccine/drug.

Adverse Vaccine Reaction (AVR): it refers to any harmful or unexpected reactions that may occur in clinical trials and be related to the study vaccine. There is at least a reasonable possibility of a causal relationship between the study vaccine and the AE, i.e., the correlation cannot be ruled out.

Serious Adverse Event (SAE): it refers to the adverse medical event that causes death, is life-threatening, leads to permanent or serious disability or incapability, requires hospitalization or prolonged hospitalization, and results in congenital abnormalities or birth defects after the participants receive the study drug/vaccine.

Advent Events of Special Interesting (AESI): refers to the adverse event of special scientific and medical interest to a product or project, which may or may not be a serious event. The investigator should be able to monitor them on an ongoing basis and report them promptly to the sponsor. For applicable AE, the investigator should investigate further to describe and understand them. Depending on the nature of the event, the sponsor may also need to communicate and/or report it to other interested parties.

Suspected Unexpected Serious Adverse Reaction (SUSAR): it refers to suspected unexpected serious adverse reactions whose clinical manifestations are beyond the

---

Investigator's Brochure for the study drug/vaccine, package inserts for marketed drugs/vaccines, summary of product characteristics, and other existing information in terms of their nature and severity.

Adverse Events Following Immunization (AEFI): It refers to the reaction or event suspected to be related to vaccination after vaccination.

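### Section 4.2.2 requires hospitalisation for any suspected or confirmed COVID-19 case, while 6.6, 11.3.2 and the synopsis make hospital care conditional; the effect on SAE counts is narrow

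*Protocol*

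**What the plan says.** **Risk section.** Protocol 4.2.2, on antibody-mediated enhancement and vaccine-enhanced disease, opens its rule with "If a subject reports a suspected or confirmed case during the study" and continues that "he/she will be required to go to the study-designated research center or hospital for hospitalization". It sets no condition on severity, test result or time since vaccination.

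**Operating sections.** In 6.6 a suspected case starts with "Any possible signs or symptoms related to COVID-19 appear", with respiratory symptoms, or with clinical or imaging evidence of pneumonia. The action is a throat swab. After a positive test, 6.6 says to "Instruct the participant to observe and record symptoms and self-medication at home, or guide him/her to go to the designated hospitals for medical treatment", depending on the situation. Section 11.3.2 says the same: "guide them to observe and record symptoms and self-medication at home, or guide them to seek medical treatment at designated hospitals". Both also direct the participant to a designated hospital for a chest CT and continue twice-weekly remote visits. After two negative tests the participant returns to routine monitoring. The synopsis repeats this pathway, and 11.2.7 refers routine and case surveillance to 6.6.

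**SAE rules.** Section 12.1 includes among the SAE criteria an event that "requires hospitalization or prolonged hospitalization". Section 12.5.1 adds that, for a participant diagnosed with COVID-19 who meets the SAE standard, the event *may not* be reported as an SAE; worsening of an underlying disease must still be reported. Section 6.2.2 lists SAE incidence over 6 months as a safety endpoint, and 11.8.2.5 compares the incidence of all SAEs between groups by Fisher's exact test.

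**The concern.** The two sets of instructions concern the same people at the same moment. One makes admission compulsory; the other leaves it to the situation and, for suspected cases, does not mention it. A site that follows 6.6 departs from 4.2.2, and the reverse. Section 4.2.2 also presents the admission rule as part of the close monitoring that answers the risk of vaccine-enhanced disease, so the risk section describes a safeguard that the operating sections do not provide.

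There is a smaller statistical side. Hospitalisation is an SAE criterion, so where no exemption applies, the pathway a site follows can decide whether an illness enters the between-group SAE comparison.

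**Working it through.** **1. Inputs (protocol 6.5.1).** 162 confirmed cases; control incidence 9%; VE 60%; 1:1 allocation; 1,286 evaluable and 1,600 enrolled per group.

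**2. The plan's own figures reproduce.** Expected vaccine-group incidence is 0.09 × (1 − 0.60) = 0.036. The sum over the two groups is 0.09 + 0.036 = 0.126, and 162 / 0.126 = 1,285.7, which rounds up to the stated 1,286. An exact conditional test on the case split, with p0 = 0.7/1.7 = 0.4118 under VE 30% and p1 = 0.4/1.4 = 0.2857 under VE 60%, gives for 162 cases a critical value of 54 vaccine cases, a one-sided alpha of 0.0247 and power of 0.922. The stated 90% is met. The present point disputes none of these figures; they only set its scale.

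**3. The passages side by side.**

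| Situation | 4.2.2 | 6.6, 11.3.2, synopsis |
|---|---|---|
| Suspected, not yet tested | Hospitalisation required | Swab; no admission mentioned |
| Suspected, two negative tests | No release from the rule stated | Back to routine monitoring |
| Test positive | Hospitalisation required | Home or designated hospital, as the situation requires; chest CT; remote visits twice a week |

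The first and third rows conflict directly. In the second, 4.2.2 is silent on when its rule would end.

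**4. How many participants.** With equal follow-up in the two groups, 162 cases at VE 60% split as:
- placebo: 162 × 1/1.4 = 115.7, about 116;
- vaccine: 162 × 0.4/1.4 = 46.3, about 46.

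This is a floor. The primary endpoint counts cases only from day 14, while 4.2.2 applies throughout the study, and 162 is stated as a minimum. Test-negative suspected cases come on top; the protocol gives no figure for them.

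**5. What reaches the SAE count.**
- *Confirmed cases.* A primary-endpoint case under Appendix 1 has symptoms and a positive nucleic acid or antigen test, so it is diagnosed COVID-19 and falls under 12.5.1. If *may not* means must not, the COVID-19 illness itself adds about 0 reported SAEs whichever pathway is followed. If it means need not, the number depends on each investigator's choice. Section 11.8.2.5 analyses all SAEs and does not mention the exemption.
- *Suspected cases never diagnosed.* Section 12.5.1 does not cover them. If admitted under 4.2.2 they would, on its face, meet the hospitalisation criterion in 12.1; under 6.6 they would simply resume routine monitoring. No passage says whether an admission made only because the protocol requires it is one that the event itself required.

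**The case against.** The strongest reply is that the working procedure is clear. Section 4.2.2 is a background risk section, whereas 6.6, 11.3.2 and the synopsis agree with one another and 11.2.7 points surveillance to 6.6. The sentence in 4.2.2 is also loose: it names a research center as a place for hospitalisation, although the site facilities listed in 13.1 include no inpatient ward. A wording or translation slip is plausible. This makes mass admission unlikely in practice, but it is an inference. The sentence is written as a requirement and no passage withdraws or limits it, so the inconsistency stands.

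The reply succeeds against three stronger readings that a reader might infer.
- *Every primary-endpoint case would become an SAE under 4.2.2, giving a split of about 116 against 46.* The documents do not support this. Those are confirmed cases, the group that 12.5.1 addresses, so the figures are admissions under a literal 4.2.2, not reported SAEs. SAE incidence would in any case be taken over the safety set of vaccinated participants (1,600 planned per group), not the 1,286 evaluable for efficacy.
- *Sections 6.6 and 11.3.2 simply send cases home.* They offer home or a designated hospital and arrange a chest CT.
- *Compulsory admission would suppress symptom reports and so bias the primary endpoint.* Nothing in the protocol shows this. Investigators ask about symptoms twice a week in the main surveillance period, on-site visits check for them, and evidence of pneumonia is a separate trigger for a swab.

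**Conclusion.** The contradiction over care is real. Read literally, 4.2.2 cannot be followed together with 6.6, 11.3.2 and the synopsis, and the conflict would arise for at least the 162 planned confirmed cases plus an unstated number of suspected cases that test negative. The split of about 116 and 46 rests on the protocol's VE of 60% and on equal follow-up in the two groups; the total of 162 does not depend on the split.

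The effect on the SAE comparison is limited to two points. Suspected cases admitted under 4.2.2 but never diagnosed would appear to meet 12.1, and their number cannot be derived from the document. In addition, *may not* in 12.5.1 can mean need not or must not, which leaves open whether COVID-19 admissions enter the Fisher comparison of all SAEs. It would go too far to say that the SAE comparison as a whole has no fixed meaning. Sample size, power and alpha are unaffected.

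**What to change.** 1. Reconcile 4.2.2 with 6.6, 11.3.2 and the synopsis so that one pathway applies to suspected cases and one to confirmed cases. The clinical team must decide which; this review takes no position.
2. State in 12.1 or 12.5.1 whether an admission made only because the protocol requires it counts as an SAE, including for suspected cases that test negative.
3. Replace *may not* in 12.5.1 with wording that says either that such events need not be reported or that they must not be, and align the SAE endpoint in 6.2.2 and the analysis in 11.8.2.5 with it, saying whether exempt COVID-19 events are in or out of the count.

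The cost is a text amendment to the protocol, with no change to design or sample size. Whether the consent text needs a matching change cannot be judged here, because the consent pages are not shown.

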#### **4.2.3. Other potential risks**

According to the Safety Platform for Emergency vACcines (SPEAC) public information, several rare diseases are associated with the COVID-19 vaccine, including neurological disorders, vascular disorders, and cardiac disorders. These diseases can be categorized as adverse events of special interest (AESI).

Neurologic, vascular, and cardiac risks will be closely monitored in this study. Based on the data from the pre-study vaccine trial, no evidence of the above risks of special

---

concern was observed in the subjects. Subjects will be closely monitored throughout this study from the first dose to the end of the study to ensure subject safety.

#### **4.2.4. Risk of blood collection**

Venipuncture is a routine clinical procedure for obtaining blood samples. Venepuncture may cause mild pain. Skin/soft tissue infections at the puncture site or in the vein are very rare. The total volume of blood collected in this study will not be detrimental to the health of the subjects.

#### **4.2.5. Risk of disclosure of personal medical information**

The personal information and privacy of all subjects will be kept strictly confidential with the following safeguards: 1) access to study documents and personal information will be limited to investigators, clinical medical research ethics committees, regulatory agencies, and funders; 2) study information materials will be kept in a locked room; and 3) all information or samples delivered to the outside of the study site will be labeled with a unique study identifier number, and personally identifiable information will be declassified.

### **4.3. Benefits assessment**

Subjects' personal information will be kept confidential.

1 All subjects will be examined (including but not limited to routine physical examination, vital signs, etc.) and the results will be provided free of charge. Adverse events following vaccination will be closely monitored by the investigator throughout the study. Appropriate and adequate medical treatment will be provided to subjects if needed.

1 Subjects may not directly benefit from receiving the study vaccine, but by participating in this study, they can contribute to the marketing of mRNA vaccines,

---

which will help more people prevent diseases associated with SARS-CoV-2 infections.

#### **4.4. Benefit/risk assessment**

Because the preventive effect of the study vaccine against disease caused by SARS-CoV-2 infection, same as any other study vaccine, may not be 100%. Because it is possible that subjects may enter the placebo group and may not develop protection against SARS-CoV-2 infection after vaccination, there remains a risk of morbidity from natural infection with SARS-CoV-2.

Based on the following considerations, participation in this study subjects exposed to a low risk of developing unknown adverse reactions.

- 1) According to the animal toxicity test of this product suggests that the safety risks associated with it can be minimized during clinical studies by following the vaccination dose and vaccination protocol specified in the study protocol and by close monitoring.
- 2) The clinical study protocol establishes strict criteria for termination/suspension of the study.
- 3) During the study, the investigator will focus on the safety evaluation and the solicited local adverse events, solicited systemic adverse events, and other adverse events after vaccination. Risk control measures, including appropriate enrollment and exclusion criteria, close monitoring of subjects, and suspension/early termination criteria, will be established before the study begins to ensure maximum benefit to the subjects.

---

Based on these safeguards, the potential risks associated with the study vaccine are reasonable concerning the benefits that could be realized for the prevention of COVID-19 in subjects.

#### **4.5. Summary**

In summary, this product demonstrated good safety and immunogenicity in non-clinical animal studies. With the continuous discovery of SARS-CoV-2 mutant strains, the effectiveness of the existing marketed vaccines against the mutant strains has declined. Moreover, as the vaccination rate of SARS-CoV-2 vaccines has increased in various countries, domestic and foreign experts have gradually begun to explore the impact of booster vaccination with multiple technical routes of SARS-CoV-2 vaccines on immunogenicity. Considering the relatively good safety of the inactivated vaccine and the decline in neutralizing antibodies over time, the sponsor plans to administer a booster dose of the SARS-CoV-2 variant (Omicron BA.5) mRNA vaccine (LVRNA012) or a placebo to those who have already received 2 or 3 doses of the novel inactivated coronavirus vaccine to assess the effect of the SARS-CoV-2 variant (Omicron BA.5 mRNA vaccine (LVRNA012), and also to observe the immunogenicity of some of the subjects, to provide a confirmatory basis for the efficacy and safety of the sequential booster vaccination with the SARS-CoV-2 mRNA vaccine.

